## Safety analysis

Safety data will be summarized for all patients who received at least one administration of IMP. AEs and SAEs will be summarized per cycle and overall using frequency tables. Also, the number and percentage of patients with AEs of grades 3 to 5 will be presented.

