## Secondary objectives

The secondary objectives of the study are:

1. To identify the proportion of patients who remain progression free at 3 years.
2. To explore changes in PD-L1 expression and T-cell infiltration.
3. To evaluate the safety and tolerability of mFOLFOX-6/avelumab.
4. To assess the quality of life of the patients in a neoadjuvant setting with avelumab.

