## 8.2. Schedule of visits

The study flowchart (Table 1) lists all of the assessments and indicates with an “X”, the visits when they are performed. All data obtained from these assessments must be supported in the patient’s source documentation.

After enrolment, all patients will be treated with IMP. The start of radiation therapy corresponds to D1 (week 1), and IMP administration at D15 ± 3 days (week 3).

During all visits, all relevant data are to be collected in the eCRF.

### 8.2.1. Selection/patient recruitment: visit 1

Patients who fulfil the eligibility criteria will be informed of all details concerning the study. Only those who agree to participate in the study and sign the informed consent will be enrolled.

Study-related procedures such as IMP administration can be only undertaken after the obtainment of the informed consent.

The visit procedures are as per the following points:

- - 1. Informed consent
    2. Verification of selection criteria
    3. Patient number:
    - Each patient in the study is uniquely identified by a 6-digit patient number which is a combination of his/her 3-digit center number and 3-digit subject number.
    - The center number is assigned by the Principal Investigator to the investigative site.
    - Upon signing the informed consent form, the patient is assigned a patient number by the Investigator.
    - At each site, the first patient is assigned patient number 1, and subsequent patients are assigned consecutive numbers (e.g. the second patient is assigned patient number 2; the third patient is assigned patient number 3).
    1. Medical history
    2. Physical examination/vital signs/weight
    3. Laboratory tests:
    - Hematology assessments: complete blood count (CBC)
    - Blood chemistry: blood urea nitrogen (BUN), creatinine, electrolytes, SGPT, SGOT, GGT, alkaline phosphatase, bilirubin
    - Virology:
      - - HBV surface antigen and HCV antibodies
        - Conduct of HCV PCR for patients positive for HCV antibodies (to differentiate active infection from past infection with HCV)
    - Urine or serum pregnancy test for women of childbearing potential who are sexually active
    - Free T4 and TSH
    - Tumor markers (CEA and CA 19-9)
    1. Baseline biopsy to evaluate:
    - PD-L1 expression:
      - - Will be evaluated on tumor cells and infiltrating immune T cells.
        - Will be classified as negative or positive or not applicable (categorical variable).

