### Period of (serious) adverse event data collection

In order to ensure complete safety data collection, recording and reporting, all (S)AEs occurring during the study, i.e. after signature of the Informed Consent, including any pre- and post-treatment periods required by the protocol, must be recorded, even if no IMP was taken.

The period of safety observation for this study is from visit 2 (D1, week 1) to 3 years after the surgery (see Study Flowchart, Table 1).

**If the Investigator detects an (S)AE after the above-defined period of observation** and considers the event as possibly related to the IMP, he/she should contact the Principal Investigator to determine how it must be documented and reported.

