## Assessment of safety

Secondary safety endpoints are the frequency, severity, and attribution of adverse events related to avelumab in a neoadjuvant setting.

AEs and SAEs from all patients followed throughout the study will be recorded and reported, as described in Section 9.5, whether or not the AE was determined to be related to the administration of IMP.

Safety evaluation will include the monitoring of the following items:

- - 1. Clinical assessments

| **Clinical assessment** | **Time of assessment** |
| --- | --- |
| Routine monitoring of vital signs (heart rate, blood pressure, and body temperature) | At inclusion  Every 2 weeks± 3 days during chemotherapy  Every 3 months after surgery for 3 years |
| Weight |
| Physical examinations: total body examination (i.e., general appearance, skin, neck, including thyroid, eyes, ears, nose, throat, lungs, heart, abdomen, back, lymph nodes and extremities) and a clinical neurological examination |
| Pelvic MRI (rectal protocol) | At inclusion  Prior to surgery: pelvic MRI (rectal protocol), optional |
| CT or PET scan of the chest and the abdomen | At inclusion |

- - 1. Laboratory assessment:

| **Blood assessments** | **Time of assessment** |
| --- | --- |
| CBC, BUN, creatinine, electrolytes, SGPT, SGOT, GGT, alkaline phosphatase, bilirubin | Prior to study initiation  Start of chemotherapy  Then every two weeks ± 3 days  Then prior to surgery |
| Free T4 and TSH | At inclusion  At least every 8 weeks during treatment  At end of treatment or 30 days post-treatment safety follow-up |
| Virology | At inclusion |

- - 1. Urine or serum pregnancy test:
       - For women of childbearing potential and who are sexually active must be performed at baseline and least every month during treatment.
       - It should be negative when the patient is enrolled in the study.

Significant findings of any safety evaluation must be recorded either on the Relevant Medical History/Current Medical Conditions eCRF (if present before signing informed consent) or on the AEs eCRF (if newly occurring or worsening since signing informed consent).

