## Protocol deviations and analysis sets

All the deviations from protocol definitions will be listed and defined as major or minor deviations in the SAP.

According to the proposed analysis, the definition of analysis sets is recommended as follows:

- - 1. ITT set: all patients who received at least one administration of the IMP.
    2. Modified ITT Set (MITT): all ITT patients who received at least one administration of IMP, with (the baseline) assessment available and have undergone surgical resection. When further restrictions/qualifications are suggested, they must be specified in a protocol amendment.
    3. Full-Analysis Set (FAS): all patients who received at least one administration of IMP.
    4. Total Treated Set: all patients who received at least one administration of IMP.
    5. Per Protocol (PP) Set: all MITT patients without major deviations. These major deviations must be defined in the protocol or in the SAP.

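### The safety summary leaves out any patient who starts protocol radiotherapy but never receives avelumab, although that patient's adverse events must be recorded from D1

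*Protocol*

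**What the plan says.** Three parts of the protocol bear on this.

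- **Who is analysed.** Section 12.9: "Safety data will be summarized for all patients who received at least one administration of IMP". Section 12.4 has no wider set: "Total Treated Set: all patients who received at least one administration of IMP". The ITT set and the FAS carry the same condition, and the MITT and PP sets are subsets of it.
- **Whose events are collected, and from when.** Section 9.5.2: "The period of safety observation for this study is from visit 2 (D1, week 1) to 3 years after the surgery". The same section says that events after consent "must be recorded, even if no IMP was taken". Section 10.2 adds: "AEs and SAEs from all patients followed throughout the study will be recorded and reported", whether or not related to avelumab.
- **When avelumab starts.** Under section 8.2, radiotherapy starts on D1 and avelumab on D15 ± 3 days. The sigmoidoscopy and biopsy at D10 fall between them. The Indemnity part of section 17 lists that D10 assessment as trial-specific, not standard of care.

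Section 12.9 tabulates adverse events by cycle and overall, and counts patients with grade 3 to 5 events. The safety objective in section 2.2 is "To evaluate the safety and tolerability of mFOLFOX-6/avelumab".

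**The concern.** Protocol treatment begins about two weeks before the dose that admits a patient to the safety analysis. Section 5.4 allows discontinuation for an adverse event, so an event in that window can itself keep the patient out of the safety population. A serious complication of radiotherapy or of the research biopsy would then be captured in the eCRF and appear in no planned summary. Section 8.1.4 rules out replacement of early withdrawals, so in a trial of 44 each such patient is a visible share of those treated.

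What is at stake is the description of the whole sequence. The trial's title and the benefit/risk section (9.2.3) speak of avelumab with mFOLFOX-6 after short-course radiation, and a reader of the report will take the safety tables to describe that sequence.

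**Working it through.** **Step 1: can a patient fall through?**

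| Patient | Events recorded (9.5.2) | In a set of 12.4 | In the 12.9 summary |
|---|---|---|---|
| Radiotherapy, then avelumab | yes, from D1 | yes | yes |
| Radiotherapy ± D10 biopsy, never avelumab | yes, from D1 | no | no |

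For the first row, nothing in 12.9 removes events that precede avelumab. They can enter the overall and grade 3 to 5 tables, but the per-cycle layout has no slot for them because cycle 1 begins with the first avelumab and mFOLFOX-6 administration. The second row is the gap.

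**Step 2: inputs.** The protocol states neither how many patients will miss avelumab nor an expected adverse event rate, so there is no planned figure to reproduce for this point. It does give enrolment (44) and the number needed for the primary analysis (36), both in section 12.2. The 44 follows from 36 × 1.20 = 43.2, rounded up. The allowance of 44 − 36 = 8 covers every reason for not being evaluable, so it serves as a high scenario for missing avelumab, reached only if all 8 stopped before the first dose.

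Assumptions:
- k, patients irradiated but never given avelumab: 1, 2, 4 or 8.
- Grade 3 to 5 rate among avelumab-treated patients: about 30% or 50%.
- y, the number of the k patients with such an event: 0 to k.

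**Step 3: formula.** With x affected patients among the 44 − k treated:

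- rate as planned = x / (44 − k)
- rate in all who started radiotherapy = (x + y) / 44

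The second exceeds the first only if y/k > x/(44 − k), that is, only if the omitted patients have the higher event rate.

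**Step 4: results.**

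| k | As planned | All started, y = 0 | All started, y = k |
|---|---|---|---|
| 1 | 13/43 = 30.2% | 13/44 = 29.5% | 14/44 = 31.8% |
| 2 | 13/42 = 31.0% | 13/44 = 29.5% | 15/44 = 34.1% |
| 4 | 12/40 = 30.0% | 12/44 = 27.3% | 16/44 = 36.4% |
| 8 | 11/36 = 30.6% | 11/44 = 25.0% | 19/44 = 43.2% |
| 1 | 22/43 = 51.2% | 22/44 = 50.0% | 23/44 = 52.3% |
| 2 | 21/42 = 50.0% | 21/44 = 47.7% | 23/44 = 52.3% |
| 4 | 20/40 = 50.0% | 20/44 = 45.5% | 24/44 = 54.5% |
| 8 | 18/36 = 50.0% | 18/44 = 40.9% | 26/44 = 59.1% |

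With k = 0 nothing changes. Otherwise the percentage can fall or rise. The count of affected patients (x against x + y) can only be too low.

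**The case against.** The best defence is that the population matches the stated target. The objective concerns mFOLFOX-6/avelumab, and the endpoint in section 3.2 concerns events related to avelumab. A patient never exposed to avelumab cannot contribute one. This stands for those tables, and the avelumab-treated set should be kept for them. It does not answer where the other recorded events go.

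Second, collecting more widely than one tabulates is not in itself a contradiction. The sentence in section 10.2 points to section 9.5, which deals with recording and reporting procedures. That is fair, so the point is best described as a gap in the planned summaries rather than a clash of rules.

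Third, section 8.2 says: "After enrolment, all patients will be treated with IMP". This is an expectation. The recording rule in section 9.5.2 provides for patients who take none.

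Fourth, early events would not go unseen. SAEs are reported immediately (9.5.4), the DSMB receives patients' safety data without an avelumab condition (3.5), and reasons for discontinuation are documented in a narrative (5.4). This limits the harm during the trial but does not put the events into the safety summary.

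A reader might go further and infer that toxicity is understated. The documents do not support that: omission removes denominators as well as events, and section 5.4 lists many reasons for leaving other than toxicity, such as withdrawn consent or loss to follow-up. A reader might also infer that events before D15 are lost for everyone. They are not, as Step 1 of the working shows.

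**Conclusion.** The gap is real and comes from a population rule that the protocol itself states, so it is not a detail left open for the SAP. Patients who start protocol radiotherapy but never receive avelumab enter no planned safety table, and toxicity can be the reason they are missing.

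Its size is unknown and may be nil. Under the assumed 4 such patients and a 30% rate in treated patients, the overall rate would lie between 27% and 36% instead of 30%. Those limits assume that none or all of the 4 had a grade 3 to 5 event. The safety of the full sequence may therefore be misstated in either direction, while the number of affected patients can only be too low. The primary endpoint is not touched. This is an inexpensive improvement and does not invalidate the planned safety analysis.

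**What to change.** In section 12.9, add a summary of AEs and SAEs from D1 for all patients who started any protocol treatment, radiotherapy onward. Show the pre-avelumab period separately, ahead of cycle 1. Because the first dose may fall on D15 ± 3 days, end that period at the actual first avelumab dose, and at a stated day for patients who never receive it. Define the matching analysis set in section 12.4.

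Keep the avelumab-treated set for the mFOLFOX-6/avelumab, avelumab-attributed and per-cycle tables.

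The cost is a wording change in the protocol and SAP and one extra table or column. The events are already collected from visit 2, so no new assessment is needed.

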## Pharmacokinetics, PK/PD, and analysis

Not applicable.

# STUDY REPORT

A clinical study report, will be prepared in accordance with the ICH-E3 guidelines, by the Principal Investigator or subcontractor in collaboration with the Principal Investigator and, if any, with the scientific committee.

Within 1 year after the end of the study, the Principal Investigator will provide the Health Authorities with the full study report or summary. Only the Principal Investigator is entitled to make the study report available to the Authorities.

Neither the complete report nor any part of the study report may be used without the approval of the Principal Investigator.

# CONFIDENTIALITY AND PUBLICATION

## Patient confidentiality

Patient data will be kept strictly confidential and patient anonymity will be protected by using number codes and initials.

The Principal Investigator, Phoenix Clinical Research and the Health Authorities will not disclose any personal patient information.

## Use of information

The Investigator shall not disclose unpublished data or information related to the study provided by the Principal Investigator, including but not limited to the study product characteristics, the IB, the study protocol, CRF/eCRF, assay methods and scientific data, to any third party without written approval from the Principal Investigator.

In addition, any new information that may become available during the course of the study shall be considered as confidential and shall not be used for any purpose other than the performance of the clinical study.

The study data are the property of the Principal Investigator. The co-Principal Investigators and the Investigators and any of the research staff shall obtain written approval from the Principal Investigator prior to the publication/communication of the results of any work carried out during or in relation to the study.

Publication and/or communication of the results of the clinical study is the responsibility of the Principal Investigator. It will be of a cooperative nature involving authors representing the Principal Investigator, the Investigators and the scientific committee, if any.

The Principal Investigator reserves the right to request modification of the content and/or timing of any publication or presentation if a patent application, an existing patent or other proprietary rights may be jeopardized.

Authorship of any publication related to the study and the order of presentation of the authors’ names shall be approved by the Principal Investigator. The Principal Investigator shall not use an Investigator’s name in any publication without his/her written permission and vice versa.

Under all circumstances, the Principal Investigator should revert back to Merck’s approval for publication.

# ARCHIVING

The Investigator must retain all study documents for 15 years or longer if required by specific local requirements. These documents include but are not limited to signed protocol, IB, CRFs, medical records, laboratory reports, informed consent forms, drug disposition records, safety reports, information regarding participants who discontinued, and other relevant documents and data.

The study-related documents should be kept together in the ISF provided to the Investigator by the Principal Investigator.

Sufficient information about the identity of all study patients, e.g. name, medical records number, patient number and study number, should be retained by the Investigator so that any Principal Investigator representatives, auditors or inspectors may access this information when required.

The Investigator will contact the Principal Investigator for authorization prior to the destruction of any study records or in the event of accidental loss or destruction of any of them.

The Investigator will also notify the Principal Investigator should he/she relocate or move the study-related files to a location other than that specified in the Principal Investigator Study Master File.

All records should be kept in a secure area. In the cases of audit or inspection, they should be easily made available.

# RESPONSIBILITIES OF PARTICIPANTS

## Responsibilities of the investigator(s)

The Investigators will conduct the study in accordance with ICH-E6, all applicable laws in the country where the study is conducted and in accordance with this study protocol.

The responsibilities of the Investigators are summarized below but not limited to:

Patient information and consent:

- 1. Prior to undertaking any study-related procedure, it is the responsibility of the Investigator, or a formal designee, to provide each patient with relevant, comprehensive, verbal and written information, including the written information which received approval or a favorable opinion from the IEC/IRB and the Health Authorities.
  2. Signed informed consent must be obtained prior to undertaking any study-related procedure. Obtaining of consent and how it was obtained must be described and documented in the patient’s file.

Adverse events:

- 1. The Investigator is responsible for ensuring adequate safety monitoring and follow-up of the study patients.
  2. The Investigator must report and handle any serious and non-serious AE, whether clinically observed or spontaneously reported by the patient, using concise medical terminology

Data recording:

- 1. It is the Investigator’s responsibility to ensure, on an on-going basis, completion and validation of all case report forms as well as study-related supportive data. The eCRF must be signed by the Investigator. If the Investigator formally delegates completion of the eCRF, the Investigator nevertheless has the final responsibility for signing the eCRF to certify the accuracy and reliability of the data recorded therein.

Record retention:

- 1. To enable inspections and audits from Health Authorities or the Principal Investigator, the Investigator agrees to keep records, including the identity of all participating patients, i.e. sufficient information to link records, all original signed informed consent forms and copies of all CRFs and detailed records of treatment disposition. The Investigator should maintain a site file with all essential documents.

Use of study-related information:

- 1. The Investigator is obligated to provide the Principal Investigator with complete test results and all data derived from the study.
  2. Only the Principal Investigator may make information available to physicians, Health Authorities and/or patients enrolled in the study, except as required by local regulations.

IMP:

- 1. Responsibility for IMP accountability at the study center rests with the Investigator or with the institution, depending on local regulations.

Quality control:

- 1. The Investigator and the relevant personnel should be available during monitoring visits and possible audits or inspections and ensure that sufficient time is devoted to the process.
  2. The Investigator guarantees the Principal Investigator or its representative and appropriate Health Authorities direct access to source documents.

Study discontinuation:

- 1. Should the Health Authorities or the Principal Investigator decide to discontinue the study prematurely for any reason, the Investigator must promptly, i.e. within 7 days, contact all participating patients so they can be appropriately followed-up. All study supplies must be collected and all case report forms must be completed as fully as possible.

Delegation of Investigator duties:

- 1. The Investigator can delegate tasks to the study team but he/she remains ultimate responsible for the study conduct. The Investigator should maintain a list of appropriately qualified persons to whom significant study-related duties will be delegated.
  2. The Investigator should ensure that all persons assisting with the study are adequately qualified, and are informed about the study protocol, any amendments to the protocol, the study treatments, and their study-related duties and functions.
  3. The Investigator, as well as the study team should supply an up-to-date curriculum vitae (CV) in English.

Study agreement discontinuation:

- 1. During the study, if events such as retirement, promotion or relocation prevent the Investigator from conducting the study as agreed, the Investigator should appropriately transfer his/her responsibilities, knowledge and documents to another willing individual, with the agreement of the Principal Investigator. Study specific contracts must be signed between the Principal Investigator and the newly assigned person.

## Responsibilities of the CRA

The responsibilities of the study CRA are defined in ICH-E6, Chapter 5. The CRA, who is mandated by the Principal Investigator, must ensure that the study is conducted in accordance with Good Clinical Practice guidelines and all applicable local laws, and that the rights, the security and the well-being of the patients are respected.

Communication:

- 1. The CRA is the main line of communication between the Investigator and the Principal Investigator.

Compliance:

- 1. During periodic monitoring visits at mutually convenient times, the CRA has the responsibility of assessing the progress of the study, of checking that the informed consent forms have been signed, of IMP accountability, of ensuring compliance with the study protocol (including storage conditions), and of ensuring the accuracy and completeness of the eCRF. Inconsistencies in the study records are to be resolved.

Source data verification:

- 1. The CRA will perform 100% source data verification and validation and request clarification to ensure the accuracy, completeness and reliability of data.

IMP:

- 1. The CRA must ensure that IMP handling is properly carried out and documented.

ISF:

- 1. The CRA must ensure that the ISF is accurately completed and up-to-date.

